### Sample size calculation

In Zhou *et al*. (2015) [32], an RCT on autistic children (average age of 4.75 years) was conducted to measure the CARS before and after the interventions in the herbal medicine–plus–behavioral education group and the behavioral education–alone group. The changes in CARS were −7.9 ± 5.42 for combination therapy and −4.6 ± 5.53 for behavioral education alone. For the purpose of calculating the standard deviation of the CARS change, the before-after correlation coefficient was assumed to be 0.33, referring to Sun *et al*. (2016) [33]. The sample size was calculated by using a two-tailed 5% significance level, 80% power, and 1:1 allocation by PASS 14 (NCSS Statistical Software, Kaysville, UT, USA). The alternative hypothesis was established that the change in CARS for 12 weeks between the experimental group and the control group was not the same. The required number of subjects per group is 45, and the total number of enrolled subjects is 120 (60 in each group), allowing for a 25% withdrawal rate.

### Statistical analysis

Data coding will be kept by the researcher team, and data analysis will be conducted by statisticians who are independent of the research team. Effectiveness data will be analyzed mainly with full analysis set (FAS) and further analyzed with per protocol set (PPS). The FAS is defined as all subjects who have taken at least one prescription in the clinical trial and have at least one measurement of the primary outcome after having the prescription. The PPS is defined as all subjects who have taken more than 118 packs (70% of the total 168 packs). The safety analysis includes all data from the participants who have taken at least one prescription in the clinical trial.

Continuous data will be presented as descriptive statistics such as mean and standard deviation, and any statistical differences between the two groups will be tested by using the independent *t* test or Wilcoxon rank-sum test. Categorical data will be presented as frequency and percentage, and any statistical differences between the two groups will be tested by using the chi-squared test or Fisher’s exact test. If significant differences of baseline are recognized between two groups, analysis of covariance (ANCOVA) or rank ANCOVA will be used. In secondary analyses within groups, continuous data will be analyzed by using the paired *t* test or Wilcoxon signed-rank test, and categorical data will be analyzed by using McNemar’s test.

The significance level is 0.05 for all statistical tests, and two-tailed tests will be performed. Missing values will be imputed by the last-observation-carried-forward method.

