### Primary outcome measures

#### Childhood Autism Rating Scale

CARS was developed to distinguish autism from other developmental disorders and to assess the severity of autism. It has high reliability, validity, and inter-rater consistency, and a cutoff score of 30 points distinguished autism from other developmental disorders. In addition, CARS reported a high rate of consistency of 92% with experts when used after short training, even if the rater has little experience with autism. In the Korean version of CARS, the internal consistency coefficient (Cronbach’s α) is 0.87, the inter-rater agreement is 0.94, and the test-retest reliability is 0.91 [20]. A total score of 30–37 indicates mild autism, and a total score of 37.5–60 indicates severe autism. In this clinical trial, the assessment will be carried out during the visit at baseline (visit 1), mid-point (visit 14), termination (visit 25), and follow-up (visit 26).

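### Baseline adjustment of the primary CARS comparison depends on a baseline significance test: an unsound trigger that forgoes available precision, though the trial stays valid and adequately powered

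*Protocol article*

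**What the plan says.** Three parts of the protocol article bear on this.

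- **Default test (Statistical analysis).** For continuous data, "any statistical differences between the two groups will be tested by using the independent *t* test or Wilcoxon rank-sum test". The section names no separate model for CARS.
- **Trigger for adjustment (same section).** "If significant differences of baseline are recognized between two groups, analysis of covariance (ANCOVA) or rank ANCOVA will be used". It does not say which baseline variables count.
- **Scale and planning values (Sample size calculation).** The alternative hypothesis is that "the change in CARS for 12 weeks between the experimental group and the control group was not the same". The planning data are: "The changes in CARS were −7.9 ± 5.42 for combination therapy and −4.6 ± 5.53 for behavioral education alone". In deriving the SD of change, "the before-after correlation coefficient was assumed to be 0.33". The design uses a "two-tailed 5% significance level, 80% power, and 1:1 allocation", giving 45 per group, raised to 60 for 25% withdrawal.

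Baseline CARS is measured in every child. The CARS section schedules it at visit 1, with the end-of-treatment score at visit 25. Nothing elsewhere in the article fixes a baseline-adjusted analysis.

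**The concern.** Under randomisation any baseline difference is due to chance, so testing it answers a question whose answer is already known. Whether adjustment helps depends on how strongly baseline predicts the outcome, and the test does not measure that.

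The conditional rule has two consequences. First, the reported treatment effect is either a raw difference in mean change or a baseline-adjusted difference, and which one appears is settled only after the baseline data are examined. Second, because the test seldom fires, the unadjusted change score is nearly always used. A change score subtracts the whole baseline value, while ANCOVA subtracts only the share the data support. When the before-after correlation is modest, as the plan assumes, the change score carries avoidable noise. What is at stake is precision in the primary comparison and a primary estimator fixed in advance.

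**Working it through.** **Inputs (Sample size calculation).** Difference in mean change 7.9 − 4.6 = 3.3; SDs of change 5.42 and 5.53; correlation ρ = 0.33; two-sided α 0.05; 45 evaluable per arm. **Assumption, not in the protocol:** the ratio k of week-12 SD to baseline SD. I take k = 1 as the base case and show a range.

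**1. Reproduce the plan's figure.** Pooled SD of change = √((5.42² + 5.53²)/2) = 5.475. For a two-sample t test (noncentral t), power is 79.8% at 44 per arm and 80.7% at 45, so 45 are needed; 45/0.75 = 60. The plan's 45 and 60 are reproduced. They are the numbers for an unadjusted t test on 12-week change, which supports reading the default test on that scale.

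**2. Precision of ANCOVA relative to change, equal SDs.** With a common single-visit SD σ:
- Var(change) = 2σ²(1 − ρ), so σ = 5.475/√(2 × 0.67) = 4.73.
- Var(ANCOVA residual) = σ²(1 − ρ²), so the residual SD = 4.73 × √(1 − 0.33²) = 4.465.
- Variance ratio = (1 + ρ)/2 = 0.665, so the change score loses 33.5% of the information.
- Power at 45 per arm is 93.4% for ANCOVA against 80.7% for change. ANCOVA reaches 80% at 30 per arm.

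**3. Sensitivity to the assumptions.** In general the ratio is k²(1 − ρ²)/(1 + k² − 2ρk). The SD of change is held at 5.475.

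| ρ | k | Ratio | Information lost by change score | ANCOVA power, 45 per arm |
|---|---|---|---|---|
| 0.33 | 0.8 | 0.513 | 49% | 97.7% |
| 0.33 | 1.0 | 0.665 | 34% | 93.4% |
| 0.33 | 1.25 | 0.801 | 20% | 88.5% |
| 0.33 | 1.5 | 0.887 | 11% | 85.1% |
| 0.70 | 1.0 | 0.850 | 15% | 86.6% |

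If the unadjusted test were applied to week-12 scores instead of change, the loss against ANCOVA would be ρ² = 0.33² = 11%, whatever k is.

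**4. The conditional rule itself.** Simulation of 100,000 trials with 45 per arm, normal data, ρ = 0.33, k = 1, and baseline CARS as the only trigger:

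| | Change-score t | Conditional rule | Always ANCOVA |
|---|---|---|---|
| Power at a difference of 3.3 | 80.7% | 82.0% | 93.1% |
| Type I error | 5.0% | 4.1% | 4.9% |

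The baseline test was significant in about 5% of trials, as it must be under randomisation. The rule therefore gains about 1 of the roughly 12 percentage points of power available.

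**The case against.** Much of the case for the plan stands.

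- **The trial is not underpowered.** The sample size was computed for the default analysis and reproduces exactly. The conditional rule reaches about 82%, above the 80% target.
- **Type I error is not inflated.** A reader might infer that a two-stage choice of test raises false positives. Taking the better of the two p values would do so (about 7.7% in the same simulation), but the protocol does not allow that choice: the switch depends on baseline data only. Applied as written, the rule is slightly conservative.
- **A flat loss of one third is not established.** That figure needs equal SDs at the two visits and a test on change. The protocol gives no single-visit SDs, the Statistical analysis section does not name the scale, and 0.33 is borrowed from another study. The CARS section reports a test-retest reliability of 0.91. This does not determine the 12-week correlation, but it makes a higher value plausible, and with it a smaller loss.
- **Chance imbalance is not an additional bias.** With k = 1 and 45 per arm, the largest non-significant baseline difference is 1.98 points, which moves the change-score estimate by 0.67 × 1.98 = 1.33 points. That is the extreme; the median absolute shift is about 0.45. The change score is unbiased over randomisation and its standard error already contains this variation, so it is the same precision loss seen from another side.
- **The entry cut does not bias the comparison.** A reader might infer bias from regression to the mean, because entry requires a CARS score of at least 30. Both arms pass the same cut, so the expected regression cancels between them.
- **Some detail belongs in an SAP.** How t is chosen over Wilcoxon, or ANCOVA over rank ANCOVA, may properly be settled there.

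The trigger is not excused in this way. The protocol states it outright, and an SAP with unconditional ANCOVA would contradict it.

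**Conclusion.** The concern holds as one of lost efficiency and a poor decision rule, and it should be fixed. It does not make the trial invalid or underpowered.

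At ρ = 0.33 and 45 per arm, prespecified ANCOVA would raise power from about 82% under the conditional rule to 93% with equal SDs. Across SD ratios of 1.5 to 0.8 the figure is 85% to 98%, and at ρ = 0.7 with equal SDs it is 87%. These results rest on the change scale implied by the Sample size calculation, normally distributed scores, and baseline CARS as the only trigger. The size of the gain varies with these assumptions, but its direction is the same in every case examined.

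**What to change.** Replace the conditional sentence in Statistical analysis with:

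> The primary analysis is ANCOVA of week-12 CARS (visit 25) on treatment, with baseline CARS and hospital (the stratification factor) as covariates, regardless of any baseline difference. Rank ANCOVA is a sensitivity analysis.

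Use the same model for each continuous secondary scale with its own baseline score, and drop baseline significance tests as a trigger for adjustment.

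The cost is one paragraph of protocol or SAP wording, agreed before unblinding. Baseline CARS and hospital are already recorded, and the sample size need not change.

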**Methods/design:**

This trial is a prospective, multicenter, randomized, double-blinded, placebo-controlled, parallel-group, clinical trial. The 4- to 6-year-old children with ASD will be randomly assigned to following groups:A UGSJB granule with acupuncture, twice daily (n = 120)A placebo group with acupuncture, twice daily (n = 120).

The following outcome measures will be used: behavior by the Childhood Autism Rating Scale, Autism Behavior Checklist, and Aberrant Behavior Checklist; social maturity by the Social Maturity Scale; quality of life by the Child Health Questionnaire and EuroQoL Five-dimension Five-level Youth; and parental stress by the Parenting Stress Index at baseline and at 6, 12, and 24 weeks after the beginning of treatment.

In addition, to evaluate safety, we will investigate the adverse reactions that may be caused by UGSJB granule. Finally, we will make an economic evaluation of UGSJB for the treatment of ASD.

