After screening, suitable participants will be randomly assigned to the 3.0 g/day UGSJB or placebo group. UGSJB granule is composed of nine herbs: Ban Xia (*Pinellia ternate*), Bai Zhu (*Atractylodes japonica*), Fu Ling (*Poria cocos*), Dang Gui (*Angelica gigas*), Chen Pi (*Citrus unshiu*), Chuan Xiong (*Cnidium officinale*), Diao Gou Teng (*Uncaria sinensis*), Chai Hu (*Bupleurum falcatum*), and Gan Cao (*Glycyrrhiza glabra*) (Table 1). Placebo granule is composed of 0.95 g lactose, 0.4 g corn starch, and 0.15 g caramel pigment to match the UGSJB. UGSJB and placebo granules were manufactured and stored by Kyungjin Pharmaceutical Co., Ltd. (Gyeonggi, Republic of Korea). The solvent used in the extract was purified water, and the ratio of extract to herbal drugs was about 12.2%. Storage, dispensation, and quality control of the UGSJB and placebo granules were carried out by a blinded pharmacist in each study center. Caregivers will be instructed to dissolve in water and administer one pack (1.5 g) of UGSJB or placebo granule after breakfast and dinner for 12 weeks, which was the period that reported effectiveness in previous studies [11, 12]. The dosage regimen was determined by referring to the authorization by the Ministry of Food and Drug Safety and the clinical judgment of Korean medicine doctors. The quantities of marker constituents per pack were 3.99 mg of glycyrrhizinate and 11.18 mg of hesperidin. Lead and microorganisms were not detected, and the concentration of arsenic was 0.33 parts per million in one pack of UGSJB. The UGSJB or placebo will be prescribed by Korean medicine doctors with more than 5 years of clinical experience. If there are any adverse events (AEs) related to UGSJB, such as pseudoaldosteronism, myopathy, allergic skin reaction, and gastrointestinal upset, that participant will stop taking medication and will receive appropriate treatment according to the severity of the AEs. The guardians should return the used as well as unopened packages to check the adherence to treatment.

**Table 1 Tab1:** Composition of Ukgansangajinpibanha granule

Plant name	Used part	Registration	Amount, grams
*Pinellia ternate* Breitenbach (Araceae)	Dried rhizome	KP	0.84
*Atractylodes japonica* Koidz. (Compositae)	Dried rhizome	KP	0.67
*Poria cocos* Wolf (Polyporaceae)	Dried scleorotia	KP	0.67
*Angelica gigas* Nakai (Umbelliferae)	Dried root	KP	0.5
*Citrus unshiu* Markovich (Rutaceae; citrus peel)	Dried fruit peel	KP	0.5

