There were a few concerns about planning the study protocol. First, there are no limitations to concurrent treatment except for risperidone and aripiprazole. Therefore, it may be difficult to manage all interventions because of the wide variation in each participant’s concurrent treatment. However, there is no standard treatment for ASD, and ASD is often treated case by case because of the broad spectrum and individual differences in symptoms. Therefore, we decided to verify the effects of herbal medicine added to acupuncture while maintaining existing treatments throughout the clinical trial, which is similar to the management protocols of clinical Korean medicine. Second, it was discussed that the subjectivity of evaluators could affect overall outcomes since all outcome variables will be obtained through questionnaires. In order to reduce this bias, we decided to use placebo to keep blinding strictly from researchers and evaluators, unlike other existing RCTs of herbal medicines on ASD. Third, owing to the intractable nature of disease, changes in symptoms may not be noticeable in the short period of 3 months. Therefore, we decided to reassess the symptoms after 3 months when the interventions are completed.

UGSJB treats aggressive behavior by suppressing excess glutamateric neuron activity in the hippocampus [37], anxiety through the serotonergic neurotransmission pathway [38], chronic pruritus by inhibiting nerve growth factor–induced neurite growth [39], and insomnia by increasing stage 2 sleep and decreasing sleep latency [40]. UGSJB has some neuronal effects and was reported to improve symptoms of ASD in a case report [41]. However, these effects have not been demonstrated in a clinical trial. Ukgansan, which is a variant of UGSJB, has shown only some experimental and anecdotal improvement of ASD symptoms. Our RCT will provide results on the safety, effectiveness, and economic value of UGSJB for ASD, and treatment options with higher evidence may be provided to children with ASD.

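### LOCF is the only stated rule for missing data, and with both arms expected to improve and 25% withdrawal planned it can bias the week-12 CARS difference

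*Protocol article*

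**What the plan says.** The Statistical analysis section of the protocol article gives a single missing-data rule for every outcome: "Missing values will be imputed by the last-observation-carried-forward method". It names no alternative and no sensitivity analysis for missing data. The FAS is the main effectiveness set and the PPS the further one. Besides one dose, entry to the FAS requires that children "have at least one measurement of the primary outcome after having the prescription".

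CARS, the primary outcome, is scored at "baseline (visit 1), mid-point (visit 14), termination (visit 25), and follow-up (visit 26"). The abstract puts the outcome measurements "at baseline and at 6, 12, and 24 weeks after the beginning of treatment". The first CARS after dosing is therefore due at week 6.

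The Sample size calculation tests the between-group difference in 12-week CARS change. It takes changes of -7.9 (SD 5.42) and -4.6 (SD 5.53) from a cited trial, and enrols 60 per group for 45 required, "allowing for a 25% withdrawal rate".

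**The concern.** LOCF is neutral only if a leaver would have stayed at the last recorded score. The plan's own figures assume otherwise, since both arms are expected to improve over 12 weeks. A week-6 value standing in for week 12 then understates the change in each arm, in proportion to that arm's late loss and its expected improvement. The arm that loses more children after week 6 looks worse than it is.

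The primary contrast is at stake. With similar loss in the two arms the effect is diluted. With unequal loss the estimate can move either way, so LOCF cannot be defended as conservative. The same rule fills missing week-24 scores, which belong to an off-treatment visit, with values recorded by the end of treatment.

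**Working it through.** **Reproducing the plan's figure.** The difference is 7.9 - 4.6 = 3.3, and the pooled SD is sqrt((5.42² + 5.53²)/2) = 5.475. At two-sided 5%, the noncentral t gives 79.8% power at 44 per group and 80.7% at 45. Then 45/0.75 = 60 per group. The stated 45 and 60 are reproduced.

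**Assumptions not in the document.** The week-6 mean change is half the week-12 change. Dropout is unrelated to outcome. The split of loss by arm and by time is chosen for illustration, because the article gives only an overall 25%. Differences below are the extra CARS reduction on UGSJB.

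**All leavers last seen at week 6.** With loss p, the LOCF mean is (1 - p) × full change + p × half change = full change × (1 - p/2).

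- 25/25%: 7.9 × 0.875 - 4.6 × 0.875 = 6.9125 - 4.025 = 2.89
- 35/15% (UGSJB/placebo): 7.9 × 0.825 - 4.6 × 0.925 = 6.5175 - 4.255 = 2.26, which is 31% below 3.3
- 15/35%: 7.9 × 0.925 - 4.6 × 0.825 = 7.3075 - 3.795 = 3.51

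**Half of leavers gone before week 6.** Those children are outside the FAS. The share of the FAS that is carried forward is q = (p/2)/(1 - p/2), and the multiplier is 1 - q/2. This is 0.9286 for p = 25%, 0.8939 for 35% and 0.9595 for 15%.

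| Loss, UGSJB/placebo | All leavers after week 6 | Half before week 6 |
|---|---|---|
| 25/25% | 2.89 | 3.3 × 0.9286 = 3.06 |
| 35/15% | 2.26 | 7.9 × 0.8939 - 4.6 × 0.9595 = 2.65 |
| 15/35% | 3.51 | 7.9 × 0.9595 - 4.6 × 0.8939 = 3.47 |

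A simulation (60 per group, 6,000 runs, t test on week-12 change, week-6 SD 0.8 of the week-12 SD, correlation 0.6) gave 2.87 for 25/25% all late. With half early it gave 3.06, 2.65 and 3.48.

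**No drug effect, both arms at -4.6.** Unequal late loss of 35% and 15% creates a false difference of 4.6 × (0.925 - 0.825) = 0.46 against the arm that loses more. The SE is 5.475 × sqrt(2/60) = 1.00. The rejection probability is P(Z > 1.50) + P(Z < -2.42) = 0.067 + 0.008 = 7.5%. Simulation of 15/35% loss gave 7.8% (all late, false difference 0.47) and 6.0% (half early, 0.30). Equal 25% loss gave 5.1%.

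**Comparator.** In the same runs, completers with no carry-forward recovered about 3.3, or about 0 under no effect, with type I error of 4.4% to 5.5%. They stand in for an analysis without carry-forward under outcome-unrelated dropout. The repeated-measures model itself was not simulated.

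**Whether the PPS offsets this.** It requires more than 118 of 168 packs. At two packs a day, 119 packs take 59.5 days, or 8.5 weeks. A child who leaves after that but before week 12 can meet the PPS criterion and still carry a week-6 CARS, so the PPS is no check on LOCF.

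**The case against.** The best case for leaving the rule alone is that the 25% is a planning allowance, no split by arm or time is given, and no time course supports linear improvement. With equal loss the bias only dilutes the effect. Simulated power then hardly suffers (81.2% with LOCF against 80.4% for completers, half of leavers early), and type I error stays near 5%. All of that stands, and it is why 2.9 to 3.1 is the lead figure and the unequal splits are shown only as a range. It does not rescue LOCF, because the trial cannot choose its dropout pattern and the rule has no stated backup.

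Four stronger readings are tempting but not supported.

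- A reader might infer that the LOCF standard error is too small, since 60 values are counted where 45 were observed (5.475 × sqrt(2/60) = 1.00 against 5.475 × sqrt(2/45) = 1.15). In simulation the model SE matched the actual spread of the LOCF estimate (1.06 and 1.06 with half of leavers early). The excess type I error came from bias under unequal loss.
- A reader might infer that a child stopped for a drug-related adverse event falls out of the main analysis. The Interventions section says "that participant will stop taking medication and will receive appropriate treatment according to the severity of the AEs". That stops medication, not assessment, and such a child seen at visit 14 stays in the FAS.
- A reader might put a size on the FAS exclusion by giving children who leave before week 6 no change from baseline. That conflicts with the improvement expected in both arms and changes the quantity being estimated, so no such figure is offered.
- A reader might see a durability claim at week 24. The Discussion gives a different reason: change may be hard to see within 3 months, so "we decided to reassess the symptoms after 3 months when the interventions are completed". The narrower point stands: for leavers, LOCF enters no change since their last score at a visit meant to detect late change.

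**Conclusion.** The concern holds as a should-fix. LOCF is a rule the article fixes, not a detail left to an unseen analysis plan, and it conflicts with the plan's own expectation of improvement in both arms. Under linear improvement, the planned 3.3 points become about 2.9 at 25% loss in both arms if every leaver is last seen at week 6, and about 3.1 if half leave earlier. Assumed losses of 35/15% or 15/35% give about 2.3 or 3.5 with all loss late, and about 2.65 or 3.5 with half early. With no drug effect, such imbalance raises type I error to about 6 to 8%; balanced loss does not. The direction therefore depends on which arm loses more children after week 6, which the documents do not predict. The sample size of 60 per group is unaffected.

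**What to change.** Replace LOCF as the primary method with a mixed model for repeated measures on the observed CARS scores at weeks 6, 12 and 24. Include treatment, visit, treatment-by-visit, baseline CARS and hospital (the randomisation stratum), and name the week-12 treatment contrast as primary. The model assumes data are missing at random given what was observed, and this should be stated.

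The model alone does not bring in children with no post-dose CARS, because they contribute nothing to the week-12 contrast. Add a reference-based multiple-imputation sensitivity analysis in all randomised children; that is the step that includes them. Keep LOCF at most as a further sensitivity analysis.

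The cost is modest programming and an analysis amendment, which under Ethics and dissemination needs the principal investigator's agreement and approval by each IRB. No visits are added, because the CARS assessments are already scheduled. The confidence interval may be slightly wider than under LOCF.
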